### Randomization and allocation concealment

2.8

Randomization will be performed at post-baseline assessment and stratified by age and sex. The random allocation sequence will be generated using the PLAN sentences of Statistic Package for Social Science 21.0 (SPSS 21.0) by an independent statistician who will be not involve in this trial. The eligible participants will be allocated to either *TCPSQ* group or unaltered lifestyle control group according to 1:1 equal proportion rule. To make sure that the risk of bias remains low, participants will be registered in the database by means of a participant ID code so that assessors are blinded during the analysis. The random allocation sequence will be managed by a specified project manager who is not involved in the recruitment program of this trail, and be concealed to the screeners and outcome assessors. Randomized group assignments were sealed in opaque white envelopes. Allocation concealment will be ensured, as the service will not release the randomization code until the participants are recruited into the trial after all baseline measurements are completed. Once participants consented to enter the trial, envelopes were opened and assignments made to *TCPSQ* group or control group. The eligible participants will be informed their allocation result by the project manager via telephone after post-baseline information assessment.

### Informed consent

2.9

Prior to the study, the general study process and the responsibilities of both participants and researchers will be explained to potential participants. They will be told that their entry into the trial is entirely voluntary and that they can withdraw at any time. In the event of their withdrawal, the data collected cannot be erased and will be used in the final analyses. Written informed consent should be obtained from each participant before any interventions related to the study are started. A research assistant will be responsible for obtaining informed consent from all participants.

### Blinding

2.10

In this trial, it is impossible to blind the participants and Qigong exercise coaches due to this being a nonpharmacological intervention trial. Nevertheless, 2 kinds of blind code will be used to blind the outcome assessors and statistician, and we will assign a specified project manager to be in charge of the management of the random allocation sequence and blind code of the participants’ allocation result will be replaced by using alphabet “A” or “B.” And the real meaning of “A” or “B” will be signed in the second blind code. A twice unclosed blind code will be performed in this trial. Firstly, after close of data-base, the project manager will deliver the group code “A” or “B” of participants to the statistician. Secondly, the project manager will declare the real meaning of group “A” or “B” after analysis of all data is completed. Furthermore, we will rule that each investigator has a well-defined obligation: the project manager and Qigong exercise coaches will not take part in the assessment of outcome; at the same time, the outcome assessors, laboratory technicians, data managers, and the statistic analyzer will be not involved in the participants’ screening and allocating. The allocation sequence and blind code will be preserved by an independent project manager who is irrelevant with the recruitment, intervention, assessment, and statistic analysis until the statistical analysis is completed.

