### Study design

2.2

This study was designed as a pilot 2-arm, randomized, assessor and statistician blinded, parallel-controlled trial comparing the beneficial effect of *TCPSQ* in college students with unaltered lifestyle control repeatedly. A total of 80 eligible college students from the Beijing University of Chinese Medicine (BUCM) will be recruited and randomly allocated to either the *TCPSQ* group or control group (unaltered lifestyle) according to 1:1 allocation ratio with allocation concealment. The participants in the *TCPSQ* group will accept a 10-week *TCPSQ* exercise training, at the same time the others in the control group will maintain their original lifestyle. The study period is 18 weeks including a 10-week supervised intervention and a 8-week follow-up with relevant physical and psychological outcomes will be measured at baseline, 6 weeks (at the mid-point of intervention), 11 weeks (at the end of intervention), and 19 weeks (after the 8-week follow-up period) by the assessors who are not participated in this trial at the Qigong and Human Science Laboratory of BUCM. The statistic analysis will be performed by special statisticians who are not involved in this trial. The flow diagram for this trial is presented in Figure 1.

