#### Control group

2.11.2

The participants in the control group will not receive any specific training. They will be informed to maintain their original daily lifestyle in the intervention period (based on the initial inclusion criteria that they were not exercising on a regular basis) and requested not to commence any regular exercise regime or participate in other mind-body exercises, such as yoga or other forms of Qigong. On the completion of the study they will be given the same 10 weeks of *TCPSQ* training after the 19 weeks so as to increase involvement compliance rate.

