#### Intervention regimen

2.11.3

*TCPSQ* training consisted of an initial workshop conducted over 3 consecutive half-days by 2 qualified coaches. Participants received concentrated training: this consisted of instruction in source of *PSQ*, understanding in the essence and beneficial effects of *PSQ*. Participants will be taught the relevant knowledge of *TCPSQ*, which includes the rationale that *TCPSQ* constitutes a health benefit, the action essence of *TCPSQ* the philosophy opinion of *TCPSQ*. The instruction of *TCPSQ* will be both verbal and visual. And participants will be also obtained information about procedure of this study, and the matter needing attention of individuals in the trial. Participants will be required to learn the key movements known as “regulating body, breathe, mind” and ancillary exercises with multiple repetitions of *TCPSQ* until they master it, as will be confirmed by the professional coaches. The coaches will visit each individual daily to ensure that the movements are being correctly practiced.

Once initial concentrated training was complete, participants were asked to practice supervised training. Participants of *TCPSQ* group will undergo the regular training together for the last 10 weeks at a frequency of 5 days per week (from Monday to Friday), training will be performed for 50 minutes per day, each session will include a warm-up for 10 minutes. Specified *TCPSQ* performed and refined for 30 minutes, the practice method successively as follows: body adjustment; breathing adjustment; mind adjustment, and cooling down for 10 minutes. The instructors will visit each individual to ensure that the movements are being correctly practiced. All participants will be required to fill self-made *TCPSQ* training self-evaluation scale (including self-evaluation of training difficulty, the relaxation or tensity or pain and fatigue of various parts of body, perspiration level, saliva secretion level, body sense of warmth, breathing control state, meditative state of mind, abnormal physical and mental reaction, level of coordination between body and mind during and after training) and record their daily PA information during the intervention period. The compliance of the subjects will be assessed in terms of the number of training attended and the number of training self-evaluation scale per day.

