### Statistical analysis

2.16

Collected data will be recorded on standardized forms. Descriptive statistics will be calculated for dependent and independent variables. This analysis will include summary statistics of demographic information and outcome measures. Continuous variables will be summarized as mean (SD) ± standard deviation for normal distribution, and median (IQR) ± interquartile range for non-normal distribution. Normality will be tested using *Kolmogorov–Smirnov* test and categorical variables will be presented with frequencies or percentages. Appropriate transformations will be applied in cases of non-normal distribution. For the variables with a normal distribution, differences in terms of outcomes between groups will be compared using an independent *T-*test. If the variables have a non-normal distribution of ordinal level, statistical comparison between groups will be made by using the *Mann– Whitney U* test even after suitable transformations. Measures with a discrete distribution will be expressed as percentages and analyzed by the *X*^*2*^ or Fisher's exact test as appropriate. Subgroup analysis will be performed according to participants’ gender, personality, and constitution of TCM. Analysis of variance (ANOVA) will be used for the repeated measurement data, and *post-hoc* comparison between groups at different assessment time points will be conducted using multiple comparisons with adjustment to the type 1 error rate. Analysis of the primary and secondary outcomes will be on the basis of intention-to-treat (ITT) population and per-protocol (PP) population. The result of the ITT analysis will be compared with that of the PP analysis to check whether the results are consistent or not. If the statistical results of the ITT and PP population data are the same, the results will be deemed to be reliable; if they are contrary, we intend to adopt the results of the ITT population. The method of processing missing data will be the last observation carried forward (LOCF). This refers to assigning the last observed value of the end point indicator to the subsequent missing evaluation point; that is, the last observation response will be considered to be the study end point. Safety will be evaluated by tabulations of AEs, and will be presented with descriptive statistics for each group. A chi-square test or a Fisher's exact test will be used to compare the frequency difference in AEs between the 2 groups, and severe AEs will be listed in detail. To explore potential factors which might influence adherence, a logistic regression model and a linear mixed-effects model will be used and adjusted for potential confounders. Adherence-related data will be taken from training log records. All statistical tests will be implemented using IBM SPSS 21.0 with bilateral inspection. The level of statistical significance is assumed at 2-sided *P* value <.05.

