*TCPSQ* is one of common forms of *PSQ*. It is characterized by 3 circles: that between the hands, the arms, and the arches of the feet, in addition to the low, medium, and high postures based on the angle of knee flexion. In terms of breath and mind adjustment, it mainly employs normal abdominal breathing and gradually increases the intensity of concentration of the mind on the lower Dantian.^[75]^ The effect of this *PSQ* on the circulatory and respiratory systems is evident. It improves respiratory efficiency and increases blood and oxygen supply in the peripheral tissues by expanding the movement of the diaphragm and regulating myptasis of the lung. Moreover, it has a comprehensive effect on the motor system, coordinating the movements of the shoulder, elbow, wrist, hip, kenn, ankle, and toe joints, and promotes return of venous blood in the lower extremities. Hence it is often used to treat arthropathy, spinal disease, microcirculatory disorders due to diabetes, and arteriolar spasm due to hypertension As an aerobic exercise, previous studies have indicated that *TCPSQ* exercise program can improve sleep quality, psychological well-being for adults.^[75–77,80,83–88]^ But there is currently a lack of evidence regarding the associations between *TCPSQ* and physical fitness, as well as self-reported symptom intensity, anxiety, depression, self-esteem, and quality of sleep. In addition, from a Qigong point of view, the content of Qigong is based on the “the 3 adjustments” of body, breath, and mind. The aim of the 3 adjustments is to achieve a state of harmonious unity-integrating these adjustments into “one.”^[40,75]^ There is a popular belief that the 3 adjustments themselves stand for Qigong. But attention needs to be paid to the rest of the definition: the state of unity. This state of oneness is the criterion that distinguishes Qigong form ordinary physical exercises, in which the 3 adjustments are practiced independently, not unified. It is believe that it is easier to achieve this state of oneness from practicing *TCPSQ.*^[75]^ However, related research is not found. In this trial, we will apply modern devices including the *Nuamps 40 channel EEG signal recording and analysis system, Footscan Balance 7.7 acquisition and recording system, Spinal-mouse Spinal morphology measuring instrument* and *MP150 multiple-channel electrophysiological recording device* to synchronously measure the change of “the 3 adjustments” of body, breath, and mind and correlation analyses state of harmonious unity-integrating these adjustments into “one” in *TCPSQ state.* Moreover, it also further compares the difference between *Qigong state* and natural state. Furthermore, we will deeply explore the influence of *TCPSQ* on college students with different personality and constitution of TCM. This trial focuses on a college student population. Through a 10-week intervention with *TCPSQ*, results from a range of primary and secondary outcome measures will provide the clear information about difference in physical and psychological outcomes between *TCPSQ* and usual unaltered lifestyle control group. In this trial, we scrupulously performed the rigorous randomized, parallel-controlled, assessor-blinded and statistician-blinded design with an appropriate sample (n = 80) to evaluate the effectiveness and safety, feasibility of *TCPSQ* on the physical and mental health of college students. We will arrange 2 qualified teachers to serve as the coaches in order to ensure the standardized intervention training for participants. Participants in *TCPSQ* group will be gathered to do the exercise at a fixed setting and time and required to fill self-made *TCPSQ* training Self-evaluation Scale. To control the trial bias, all participants in both groups will be required to record their PA and sport diary as well as the sedentary time and sleeping time everyday throughout this study. Furthermore, the result evaluators and statistical analysts will be blinded to ensure the authenticity and objectivity of the trial results.

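### Statistician blinding cannot last until all data are analysed, because the planned analyses include training data that only one arm can have

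*Protocol article*

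**What the plan says.** Section 2.10 describes a code opened in two steps. First, "after close of data-base, the project manager will deliver the group code" A or B to the statistician. Then comes the decoding: "Secondly, the project manager will declare the real meaning of group “A” or “B” after analysis of all data is completed". No class of data is exempted. Section 2.2 states who analyses: "The statistic analysis will be performed by special statisticians who are not involved in this trial". No separate unblinded analyst is named.

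Section 2.16 places several things within that analysis: primary and secondary outcomes in the ITT and PP populations, adverse-event comparisons, and logistic and mixed-effects models of adherence. On the source for the last of these it says: "Adherence-related data will be taken from training log records". Section 2.11.3 defines compliance: "The compliance of the subjects will be assessed in terms of the number of training attended", together with the number of training self-evaluation scales completed. Section 2.13.4 lists the Qigong training self-evaluation scale (SQTSS) as a secondary outcome, with one subscale for the time during training and one for the time after it.

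Of the controls, section 2.11.2 says: "The participants in the control group will not receive any specific training". They are offered the same 10 weeks of training only after week 19. The Discussion presents the blind as a safeguard: "the result evaluators and statistical analysts will be blinded to ensure the authenticity and objectivity of the trial results".

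**The concern.** A letter code conceals allocation only while nothing in the analyst's dataset reveals which letter is which. Here the blind is meant to last through every analysis, yet some of those analyses use data generated by the intervention itself. The statistician cannot carry out the full plan and stay blind until its end.

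This matters because participants and coaches are unblinded and several primary outcomes are self-reported. The Discussion offers the blinding of assessors, technicians, data managers and statisticians as mitigation. Blind analysis protects choices made after the data are seen. If the letters can be read before the outcome comparisons are settled, that protection may be missing where the article says it exists.

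**Working it through.** No formula applies, and the plan gives no figure to reproduce. The check sets the sections side by side.

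1. **What the statistician holds, and when.** Participant-level letters from database close, with their meaning withheld until every analysis is done (2.10).
2. **What falls within those analyses.** Adherence models fed by training logs (2.16), and secondary outcomes under ITT and PP (2.16), one of which is the SQTSS (2.13.4). The overlap is therefore in a listed outcome as well as in an exploratory adherence model.
3. **Who can have such data.** Attendance needs sessions. The regimen in 2.11.3 is 5 days a week for 10 weeks, that is 5 × 10 = 50 scheduled sessions per TCPSQ participant. Controls have 0 up to week 19 (2.11.2).
4. **Who fills in the training scale.** Section 2.11.3 speaks of all participants, but within the description of the TCPSQ regimen. The Discussion ties the scale to the TCPSQ group and, by contrast, says that activity diaries are kept in both groups.
5. **Apparent counter-evidence.**
   - Section 2.4 issues a log book to each participant, and section 2.5 makes filling out a training record form an inclusion criterion for all. The books may exist in both arms, but controls have no sessions to enter.
   - Section 2.13.3 describes another scale, on the internal-operation state at testing, where controls imitate recorded instructions. Both arms appear to complete it, so its presence reveals nothing.
   - The measurement schedule (Table 1) is not visible in the text at hand. Whatever it shows, untrained controls cannot have attendance records.
6. **Consequence.** A tabulation of attendance, training-log content or SQTSS by letter gives one filled column and one that is empty or zero. This identifies the arms before the decoding step in 2.10.
7. **Other revealing items.** One withdrawal reason in 2.7 applies only to controls (regular practice of TCPSQ). Adverse-event causality in 2.14 refers to the intervention. Either can reveal an arm if exported with the letters.
8. **What remains open to choice.** Section 2.16 fixes ITT as the result to adopt if ITT and PP disagree. It also ties the test to a Kolmogorov–Smirnov check, then transformation, then Mann–Whitney if needed. The form of the transformation is not fixed. That, with related modelling choices, is the discretion that blinding would protect.

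**The case against.** The strongest reply is that the order of analyses and the content of data exports belong in an analysis plan or data-management plan, which is not at hand. The article does not say that training data are joined to the letters before the outcome comparisons. Section 2.15 has the project manager, who holds the code, prepare the data, so training data could be kept apart. The adherence question concerns the trained group and needs no A-versus-B contrast.

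Much of this stands. A reader might infer that the statistician is necessarily unblinded while the outcome comparisons are run, so that the code conceals nothing. The documents do not support that, because they state no such order; with the two-arm outcomes analysed first, the blind could hold for them. A reader might also infer that the choice between ITT and PP, or between t-test and Mann–Whitney, is left to an unblinded analyst; section 2.16 sets a rule for both. Finally, 50 sessions × 40 participants = 2,000 scheduled attendances against 0 might be taken as the size of the problem. It shows how readily the arms could be told apart, but measures no bias.

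What the reply does not remove is the rule in 2.10 itself. It fixes a single decoding point after all data, and an analysis plan that decoded earlier for the adherence work would contradict it. The SQTSS is also a secondary outcome, so it cannot be set aside as a purely exploratory item.

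**Conclusion.** The point holds in a limited form. Statistician blinding through the analysis of all data is a property this design does not have, because part of those data has content in one arm only. Whether the blind also fails for the two-arm outcomes depends on an order of analysis that the article neither states nor requires.

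The effect on results is unquantified, and nothing here shows that bias has occurred or will occur. The exposed discretion is narrow: mainly the form of transformation and similar modelling choices. Blinding of the outcome assessors is not touched. The trial describes itself as a pilot, and its Discussion already acknowledges the risk from unblinded participants and self-reported scales. The correction is still worth making, since the safeguard is claimed in the abstract, section 2.2 and the Discussion and costs little to secure.

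The conclusion assumes that training attendance, training logs and the SQTSS have no real content for controls before week 19, as section 2.11.2 and the Discussion imply, and that the same statistician handles those data with the letters attached, since no other analyst is named.

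**What to change.** Stage the release in section 2.10.

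1. **Before any letters are released**, someone without access to outcome results sets a yes/no per-protocol flag for each participant. Per-protocol membership is then not built by an unblinded analyst.
2. **First release:** the A/B letters with a dataset that carries this flag but omits training logs, attendance, training self-evaluation scales (SQTSS included), withdrawal reasons that reveal the arm, and adverse-event causality. On it, complete and lock the ITT and PP comparisons of the primary and secondary outcomes measured in both arms.
3. **Second release:** decode A/B and supply the training data for the adherence models, training-scale summaries and adverse-event causality tables.

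Replace "after analysis of all data is completed" with wording to the effect that decoding follows the lock of the two-arm ITT and PP outcome analyses. Limit the claim of statistician blinding in the abstract, section 2.2 and the Discussion to those analyses.

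The cost is a change of wording and one extra data export, with no change to participants, sample size or procedures. The adherence and training-scale analyses become openly unblinded. An imbalance in the per-protocol flag between letters may still hint at the arm, since compliance is counted from training, but unlike attendance records it does not by itself identify it.

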### Intervention

2.11

#### Three-Circle Post Standing Qigong group

2.11.1

The *TCPSQ* training will be performed lasting 10 weeks to the participants in the *TCPSQ* group at the gymnasiums of the university. The training scheme originated from the *TCPSQ* recorded in *Traditional Chinese Medicine Qigong*^[75]^ (“13th Five-Year” planning teaching materials of China National Higher Education of Chinese Medicine, Beijing: China Press of Traditional Chinese Medicine, chief editor: Tianjin Liu, Wenchun Zhang) and *Chinese Medicine Qigong Training Guidance*^[89]^ (Beijing: China Press of Traditional Chinese Medicine, chief editor: Yulong Wei) which not only is a kind of ancient Chinese health preserving technique but also is the basis of *dynamic Qigong*. *TCPSQ* exercise characterized by interplay between obviously bilateral symmetrical physical body posture (symmetrical arches of feet present circle, symmetrical arms present circle, symmetrical hands present circle), breathing control, a meditative state of mind, and mental focus in a harmonious and relaxed manner (Fig. 2). Two qualified coaches who have engaged in the *PSQ* education at least 10 years will correct the *TCPSQ* posture during the whole intervention period.

